### Secondary outcome measures

The secondary outcome measures of this study include the occurrence of: (1) myocardial infarction; (2) heart failure (NYHA III or IV); (3) cardiogenic shock; (4) serious bleeding necessitating hospitalization; (5) malignant ventricular arrhythmia (including ventricular tachycardia or fibrillation); (6) revascularization therapy (coronary artery bypass graft or percutaneous coronary interventions); (7) radiofrequency catheter ablation of AF; (8) changes of left atrial dimension, as measured by ultrasound echocardiography; (9) stroke; (10) cardiovascular mortality; and (11) all-cause mortality.

### Definitions

The definitions of AF are made according to 2012 HRS/EHRA/ECAS Expert Consensus [16]. Paroxysmal AF is defined as recurrent AF (at least two episodes) that terminates spontaneously within 7 days. Episodes of AF no more than 48 hours’ duration that are terminated with electrical or pharmacologic cardioversion should also be classified as paroxysmal AF episodes. Persistent AF is defined as continuous AF that is sustained beyond 7 days. Episodes of AF lasting more than 48 hours, but less than 7 days, in which a decision is made to cardiovert AF electrically or pharmacologically should also be classified as persistent AF episodes. Permanent AF refers to long-lasting episodes of AF that could be considered by any evidence as lasting longer than 1 year, or to a case of AF for which a decision has been made not to restore or maintain sinus rhythm by any means, including catheter ablation or surgery. Myocardial infarction is defined as a cardiac troponin rise accompanied by typical symptoms, pathological Q waves, ST elevation or depression, or coronary intervention. Heart failure (NYHA III or IV) requires echocardiographic evidence of reduced left ventricular ejection fraction or a diagnosis of heart failure by a cardiologist. Cardiogenic shock is defined by sustained hypotension with tissue hypoperfusion despite adequate left ventricular filling pressure. Signs of tissue hypoperfusion include oliguria (<30 ml/hour), cool extremities, and altered level of consciousness.

### Sample size calculation

The primary outcome measure is the change in the development of paroxysmal AF into persistent or permanent AF, the development of persistent AF to permanent AF, as well as the change in incidence of overall and persistent AF recurrence. Power calculations to provide estimates for the necessary sample size were conducted concerning the primary outcome measure. The sample size was estimated based on findings from the 12-month results of the J-RHYTHM II study [11], in which the incidence of persistent AF is estimated to be 6.8 % lower in the valsartan group than in the CCBs group. To ensure 80 % power at the 5 % significance level, a sample size of at least 1404 needs to be included. Considering a rejection rate of 20 %, about 1879 patients need to be approached.

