**Methods/design:**

The VF-HT-AF study is a multicenter, randomized, open-label, four-arm parallel group study with comparative evaluation of valsartan and fluvastatin as upstream therapies for the treatment of non-permanent AF complicated by hypertension. The primary outcome measure is change in the development of paroxysmal AF into persistent or permanent AF, the development of persistent AF to permanent AF, and change in incidence of overall and persistent AF recurrence, as evaluated by 7-days ambulatory electrocardiograph monitoring (Holter) and patients’ diaries during 2 years’ follow-up. Secondary outcome measures of this study include the occurrence of: (1) fatal and nonfatal myocardial infarction; (2) heart failure (New York Heart Association stage III or IV); (3) cardiogenic shock; (4) serious bleeding necessitating hospitalization; (5) malignant ventricular arrhythmia; (6) revascularization therapy; (7) radiofrequency catheter ablation of AF; (8) changes of left atrial dimension, as measured by ultrasound echocardiography; (9) stroke; (10) cardiovascular mortality; and (11) all-cause mortality. A total of 1879 patients will be investigated from 15 medical centers throughout China to obtain the relevant information.

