## Background

Atrial fibrillation (AF), the most common clinically significant cardiac arrhythmia, is associated with increased mortality and morbidity [1, 2], especially in hypertensive patients [3]. In general, hypertension is the most important risk factor for AF. Although much effort has been put into the development of an effective pharmacological treatment, several trials conducted in the USA and Europe proved that existing traditional anti-arrhythmic drugs failed to improve the prognosis of patients with AF [4–7].

Several systematic reviews and meta-analyses have confirmed anti-arrhythmic efficacy while raising concerns about adverse events and mortality [8]. In the past few years, a number of trials investigating upstream therapy for the prevention of AF have been reported [9]. Upstream therapies are long-term modulators of atrial remodeling regarding structure or function, which may change molecular expression contributing to the arrhythmia. The renin-angiotensin system (RAS) is an important therapeutic target for atrial remodeling. Angiotensin II receptor blockers (ARBs) have recently been reported to suppress AF recurrence in both paroxysmal and persistent AF in selected patients. However, recent placebo-controlled, double-blind trials with ARBs failed to show convincing results [10, 11]. Statins, as a well-established secondary prevention benefit for atherosclerotic coronary artery disease, are hypothesized to be beneficial against atrial arrhythmia, yet the data are inconsistent [12–15]. In addition, there have been little prospective and randomized studies to evaluate the effectiveness of upstream therapeutic strategies in hypertensive patients with non-permanent AF.

To confirm the effectiveness of ARBs or statins on AF in hypertensive patients, the Upstream Therapeutic Strategies of Valsartan and Fluvastatin on Hypertensive Patients with Non-permanent AF (VF-HT-AF study) will be conducted, with 1879 participants from 15 centers.

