### Statistical analysis

All analyses will be performed based on the intention-to-treat principle with differences assumed to be significant at a two-sided *P* value < 0.05.

Baseline characteristics and follow-up information will be collected for each group through the questionnaire. Absolute values for each question will be used to calculate the mean value, standard deviation, median value, percentile, number of cases, and percentages per group. Statistical significance will be evaluated by analysis of variance or Kruskal–Wallis rank sum test for continuous variables and chi-squared test for categorical variables, respectively. Kaplan–Meier curves will be used to describe the time-dependent occurrence of events, and the log-rank test will be performed to compare survival distributions for the four groups. To adjust for possible baseline imbalances between groups, a Cox proportional hazards model will be used. A hazard ratio will be calculated. In addition, subgroup analyses will be performed corresponding to the nature of the data. All statistical analyses will be performed using SPSS statistical software (version 17.00, Chicago, IL, USA).

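### The target of 1879 does not follow from 1404 and a 20 % rejection rate, and the article counts 1879 as patients approached in one place and as participants in another

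*Protocol article*

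**What the plan says.** The section Sample size calculation gives three linked figures. The base, for 80 % power at the 5 % level, is that "a sample size of at least 1404 needs to be included". The adjustment is introduced with "Considering a rejection rate of 20" per cent. The result is that "about 1879 patients need to be approached".

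The same total appears twice more with a different meaning. The Background says the study will be run "with 1879 participants from 15 centers". The Methods/design paragraph of the Abstract says "A total of 1879 patients will be investigated from 15 medical centers throughout China".

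The article does not define the rejection rate. It could be refusal before randomisation or loss after it. No section separately states how many patients are to be randomised.

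**The concern.** There are two linked faults. First, the article states a base, a rate and a result, and the result does not follow from the other two. At least one of the three is wrong, or a step is not shown.

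Second, one figure is given meanings that cannot all hold. People who are approached and decline are not participants. If 1879 counts approaches, the randomised number is smaller. If it counts participants, the sample size section describes it wrongly.

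What is at stake is the headline sample size. The 80 % power claim is tied to 1404. How much room the trial has for losses over two years of follow-up depends on what 1879 counts.

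**Working it through.** **Inputs.** Base 1404, rate 20 % and target 1879, all from Sample size calculation. Allocation is 1:1:1:1 (Study design), so 1404 is 351 per arm if it is the four-arm total.

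**Attempt to reproduce 1879 from 1404 and 20 %.**

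| Method | Formula | Result | Shortfall from 1879 |
|---|---|---|---|
| Standard inflation | 1404/(1 − 0.20) | 1755 | 124 |
| Common shortcut | 1404 × 1.20 = 1684.8 | 1685 | 194 |
| Standard, rounded up per arm | 351/0.80 = 438.75, so 439 × 4 | 1756 | 123 |
| Shortcut, rounded up per arm | 351 × 1.20 = 421.2, so 422 × 4 | 1688 | 191 |

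Applying the 20 % twice overshoots: 1404/0.80/0.80 = 2194, 1404 × 1.20 × 1.20 = 2022, and 1404 × 1.20/0.80 = 2106. None of these gives 1879. The gap to the standard result is 124/1755 = 7.1 %, too large for the word *about* to cover.

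**What 1879 would imply.**

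- With 1404 as base, the rate is 1 − 1404/1879 = 25.3 %. A round 25 % gives 1404/0.75 = 1872, which is close.
- With 20 % as rate, the base is 1879 × 0.80 = 1503.2. In the other direction, 1503/0.80 = 1878.75, which rounds to 1879.

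The second line is suggestive, but the article nowhere mentions 1503. The figures alone cannot show which of the three is in error.

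**Consequence under each meaning of 1879.**

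- *1879 randomised.* A 20 % loss leaves 1503, which is 99 above 1404. The trial could lose 25.3 % before falling to 1404.
- *1879 approached, with 20 % refusing.* About 1503 are randomised. Later loss could reach 1 − 1404/1503.2 = 6.6 % before the number falls below 1404. This assumes that 1404 means patients with usable outcome data.

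The randomised number differs by 1879 − 1503 = 376 between the two readings.

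**The case against.** The strongest reply is that the error is harmless. 1879 is larger than 1755, and the text makes 1404 a floor. The Abstract and the Background both point to 1879 as the size of the trial, so only the verb in the sample size section points elsewhere. In a condensed article, one loose verb is at least as likely as two competing targets. This stands: on that reading no power is lost relative to the protocol's own 1404. It does not remove the inconsistency, because the stated 20 % is then not the allowance used.

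The 6.6 % margin is also open to challenge, and rightly. The article says 1404 are to be included and does not say evaluable. If included means enrolled, 1503 already exceeds the requirement. The Statistical analysis section plans intention-to-treat with Kaplan–Meier, log-rank and Cox methods, so patients lost early still contribute follow-up until they are censored. The margin is therefore conditional, not a hard ceiling. It is also measured against a base that cannot be checked, because no control rate is given.

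That an article condenses a fuller protocol is no answer here. All three figures are printed, and they disagree.

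A reader might infer that the 15 centres have no defined point at which to stop recruiting. The documents do not support this, since two of the three statements give 1879 as the trial size. A reader might also object that 1879 does not divide by four. With *about* attached to the figure, and a ratio described as only initially equal, that has no consequence.

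**Conclusion.** The sample size statement is wrong as written. From 1404 and 20 % the target is 1755, not 1879: a difference of 124 patients, or an allowance of 25.3 % where 20 % is stated. The number to be randomised is also described inconsistently, and the two readings differ by 376 patients.

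It would be tempting to conclude that the trial is underpowered. The documents do not support that. On the reading favoured by the Abstract and the Background, the discrepancy is conservative. Only if 1879 are merely approached, 20 % of them refuse, and 1404 means evaluable patients does the allowance for later loss shrink to about 6.6 %.

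These conclusions take 1404 as given. If the true base were about 1503, the stated minimum would itself be too low, but that is a possibility raised by the arithmetic and not something the article says.

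**What to change.** 1. Return to the sponsor's own calculation and establish which of 1404, 20 % or 1879 is wrong, or which step is not reported.
2. State whether rejection means refusal before randomisation or loss after it. If both are expected, give a figure for each.
3. State one number to be randomised, with a derivation that reproduces, and use it in the Abstract, the Background and Sample size calculation.

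If 1404 is confirmed, the least disruptive correction is to keep about 1879 randomised and restate the allowance as about 25 % (25.3 % exactly). Keeping 20 % instead gives 1755, or 1756 with equal arms, and lowers a target of 1879 participants by 124 or 123.

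The first option needs a recheck and corrected text, with no extra patients if 1879 is already the number to be randomised. The second is more than wording, because the Trial status section says recruitment is under way. The main Methods/design section requires ethics committee approval for any protocol amendment, so that approval is part of the cost of whichever correction amends the protocol.

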### Data management

All the data will be entered and stored in a password-protected computer. To ensure high quality of the data, a double data entry method will be used. A data monitoring committee, of which at least two members will be independent of the research team, will monitor the data management process regularly. All the data will be frozen and then locked to prevent further editing after the validation by the data monitoring committee. Only the data monitoring committee, the study research assistant and the principal investigator will have access to the final data set. The protocol and statistical results will be published in a scientific journal.

### Statistical analysis

All analyses will be performed based on the intention-to-treat principle with differences assumed to be significant at a two-sided *P* value < 0.05.

Baseline characteristics and follow-up information will be collected for each group through the questionnaire. Absolute values for each question will be used to calculate the mean value, standard deviation, median value, percentile, number of cases, and percentages per group. Statistical significance will be evaluated by analysis of variance or Kruskal–Wallis rank sum test for continuous variables and chi-squared test for categorical variables, respectively. Kaplan–Meier curves will be used to describe the time-dependent occurrence of events, and the log-rank test will be performed to compare survival distributions for the four groups. To adjust for possible baseline imbalances between groups, a Cox proportional hazards model will be used. A hazard ratio will be calculated. In addition, subgroup analyses will be performed corresponding to the nature of the data. All statistical analyses will be performed using SPSS statistical software (version 17.00, Chicago, IL, USA).

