### Primary outcome measures

The VF-HT-AF study will examine whether fluvastatin or valsartan has anti-arrhythmic effects on non-permanent AF, apart from their lipid-lowering and antihypertensive effects, in comparison with dihydropyridine CCBs. Also, it will confirm whether a combination of valsartan and fluvastatin has better effects on non-permanent AF than either drug alone.

Therefore, the primary outcome measure is the change in the development of paroxysmal AF into persistent or permanent AF, the development of persistent AF to permanent AF, as well as the change in incidence of overall and persistent AF recurrence, which will be evaluated by 7-day Holter monitoring and patients’ diaries during the 2-year’s follow-up of the four treatment groups.

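### The 5% level used to size the trial covers one outcome and one contrast, but the protocol lists four primary components and four pairwise arm claims under a single P < 0.05 rule

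*Protocol article*

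**What the plan says.** **Outcomes.** Primary outcome measures (Protocol article) gives a measure with four parts. The two on progression are "the change in the development of paroxysmal AF into persistent or permanent AF, the development of persistent AF to permanent AF". The two on recurrence then follow in the same sentence: "as well as the change in incidence of overall and persistent AF recurrence". Sample size calculation repeats the list. Neither section combines the parts into a composite, names a leading part, or requires all of them to succeed.

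**Arm claims.** The opening of Methods/design sets the hypothesis that valsartan or fluvastatin does better than CCB-based therapy. Primary outcome measures adds that the trial will confirm whether the combination beats either drug alone. That makes four pairwise claims. Expected implications treats one of them, fluvastatin plus CCB versus CCB on AF recurrence, as sufficient proof for fluvastatin.

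**Threshold.** Statistical analysis sets one rule for every analysis, by intention to treat, with "differences assumed to be significant at a two-sided" threshold of 0.05. The only tests it names for time to event are a log-rank test across the four groups and a Cox model.

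**Sizing.** "Power calculations to provide estimates for the necessary sample size were conducted concerning the primary outcome measure". The input is that "the incidence of persistent AF is estimated to be 6.8 % lower in the valsartan group than in the CCBs group", and the result is: "To ensure 80 % power at the 5 % significance level, a sample size of at least 1404 needs to be included".

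**The concern.** The error rate was set for one question: does valsartan lower the incidence of persistent AF relative to CCBs? The article then puts three further components and three further contrasts on the same footing, all under the same 0.05 rule. Nothing says which result decides whether the trial succeeded.

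Two things are at stake. A chance finding in one cell could be reported as a positive primary result. And the 80% power at 5% would be read as covering claims it was not calculated for, including the fluvastatin and combination claims, for which no planning effect is given.

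**Working it through.** **1. The plan's own figure.** Four arms at 1:1:1:1 (Study design) give 1404/4 = 351 per arm. The article states a 6.8% difference and no control rate, so the control rate p₁ must be assumed, with p₂ = p₁ − 0.068. The usual formula per arm is

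n = [1.960·√(2p̄(1−p̄)) + 0.842·√(p₁(1−p₁) + p₂(1−p₂))]² / 0.068².

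At p₁ = 15.1% and p₂ = 8.3% this gives 351. With a continuity correction, 14.1% versus 7.3% does so. So 1404 fits one pairwise contrast at an unadjusted two-sided 0.05. The fit is not unique: a smaller alpha of 0.0167 returns 351 at a control rate of about 11.9%. A relative reduction of 6.8% does not fit. The step from 1404 to 1879 is a separate matter and plays no part here.

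**2. Chance of at least one false positive.** All arms are assumed equal on all components. Each arm has a standardised estimate X for each component, with correlation ρ between components within an arm. A pairwise contrast is z = (Xₐ − X_b)/√2, significant if |z| > 1.96. The four-group test uses Σ(X − X̄)² against the 5% point of chi-squared on 3 degrees of freedom. The simulation used 400,000 runs. The documents do not give ρ, so a range is shown.

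| Reading of the text | ρ = 0 | ρ = 0.5 | ρ = 0.9 |
|---|---|---|---|
| One composite, one four-group test | 5% | 5% | 5% |
| Four components, one four-group test each | 18.5% | 16.0% | 9.7% |
| One outcome, four pairwise contrasts | 16% | 16% | 16% |
| Four components, four pairwise contrasts each | 50.5% | 43.5% | 27.9% |

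Check by independence: 1 − 0.95⁴ = 18.5% agrees with the second row at ρ = 0. For 16 independent tests, 1 − 0.95¹⁶ = 56%. The simulated 50.5% is lower because contrasts share arms.

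**3. Power if four pairwise contrasts were simply corrected.** Bonferroni alpha is 0.05/4 = 0.0125. With 351 per arm, power falls from 80% to about 62% at an assumed control rate of 15.1%, and to about 66% at 14.1% (where uncorrected power at 0.05 is about 83%).

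**4. Power of factorial main effects.** With 1404/2 = 702 per level, alpha 0.025, and an assumed 15.2% versus 8.4%:

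- Full 6.8-point effect in both strata: 15.2% versus 8.4%, power about 96%.
- Both drugs have the same relative effect and multiply (ratio 8.4/15.2 = 0.553, combination 4.6%): margins 11.8% versus 6.5%, power about 88%.
- Combination adds nothing beyond either drug: margins 11.8% versus 8.4%, power about 45%.

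**The case against.** The strongest reply has three parts.

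*The family of 16 tests is not in the text.* The article speaks of a primary outcome measure in the singular and names only a four-group log-rank test for events. It never says that success in any one cell is success for the trial. This stands. A reader might infer a false-positive rate of about 44% as the trial's error rate. The documents do not support that as a fixed figure: it belongs to one reading and one assumed correlation. Persistent recurrence is part of overall recurrence and overlaps with progression from paroxysmal AF, so zero correlation is implausible. But the four-group test does not remove the problem. Run once per component it still gives about 10–19%, the text does not make it a gate for pairwise tests, and it cannot by itself answer the pairwise questions the article poses.

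*Multiplicity detail is commonly left to the analysis plan.* This is true of the method. Here, however, the article itself states one 0.05 rule for all analyses and a plural primary outcome. An analysis plan that named one outcome or split alpha would depart from the published text.

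*Adjustment across distinct treatments compared with a common control is debated.* That is fair for the two drug-versus-CCB questions. It does not cover four primary components with no stated order, or the combination claims.

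**Conclusion.** The point holds in this form: four components and four pairwise claims are placed under one unadjusted 0.05 rule, while the sizing covers one component and one contrast. The probability of at least one false-positive primary result runs from 5% to about 50%, depending on which analysis the text is taken to mean. It stays at 5% only for a single composite tested once, and the article defines no such composite.

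The figures assume equal arms under the null, normal test statistics, and a component correlation that the documents do not give. All power figures also rest on an assumed control rate.

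Two stronger conclusions are not supported. It cannot be shown that 1404 was derived with an unadjusted alpha; the figure fits that, but also fits a smaller alpha at a lower control rate. Nor can it be said that switching to factorial main effects would give about 96% power at no cost. That needs the assumed control rate, the valsartan effect carried over to fluvastatin, and no interaction. Under other plausible patterns power is 88% or 45%.

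**What to change.** In Primary outcome measures and Sample size calculation, name one primary outcome: persistent or permanent AF, which carries the variable the sample size rests on. Make overall recurrence and the separate progression components secondary. The definition should say how it applies to patients who enter with persistent AF, since for them a new persistent episode is recurrence and not progression.

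In Statistical analysis, state that the primary arm contrasts are controlled at an overall two-sided 0.05. A fixed sequence would do this: valsartan versus CCB (the sized contrast), then fluvastatin plus CCB versus CCB, then the combination versus each drug in a stated order. Each step is tested at 0.05 only if all earlier steps succeed. The first test keeps the planned 5% level and the power stated for it, with no extra patients.

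The cost is real but modest. The other components lose primary status, including AF recurrence, which appears in the trial's hypothesis. Later contrasts are confirmatory only if earlier ones succeed. The change is a protocol amendment, which the article says must return to the ethics committee. The article reports the trial as still recruiting.

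Factorial main effects with Holm are an alternative only if the sponsor is prepared to assume no interaction and say so. Power should then be quoted as the range 96%, 88% and 45% with the assumption behind each figure, not as 96% alone.

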### Study design

The VF-HT-AF study is a randomized, multicenter, open-label, and four-arm parallel study to evaluate the effectiveness of valsartan, fluvastatin or a combination of both on recurrent AF in hypertensive patients with non-permanent AF in China. After providing informed consent, patients will be randomly assigned using a computer system to one of four groups (the valsartan group, the fluvastatin plus dihydropyridine CCBs group, the valsartan plus fluvastatin group, and the dihydropyridine CCBs group) by the School of Public Health of Tianjin Medical University, initially in a 1:1:1:1 ratio. Physicians, who should be qualified medical practitioners, screen and follow up the patients in hospital outpatient or inpatient clinics. All patients’ data will be collected using a standard case report form and transmitted to the central database at the data center. All centers will be regularly monitored for source data documentation. Missing or questionable data will be completed and corrected by queries.

If the candidate patients have not taken ARBs, ACEIs or statins in the past at least 14 days, they will be directly enrolled and randomized. If the candidate patients have taken ARBs, ACEIs or statins, they will be randomized after a 14-day washout period. Baseline data will be collected after the washout period.

The initial dose of fluvastatin will be 40 mg/day at night, while valsartan will be prescribed initially at 80 mg/day. The fluvastatin dose will be no less than 40 mg/day and that of valsartan will be no less than 80 mg/day during the follow-up period. Blood pressures in each group must reach the target blood pressure, which is set at <140/90 mm Hg.

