### Follow-up

Clinical follow-up using standardized questionnaires will be performed every 3 months during the 2 years follow-up period from the assignment of each patient.

The dosages and types of all other anti-hypertensive, anti-hyperlipidemia, and anti-arrhythmic drugs used during the follow-up will be recorded for each patient. Ultrasound echocardiography will be performed before the patients enter the study and at the end of the follow-up period. 7-day Holter monitoring will be performed at the baseline, 6 month, 12 month and at the end of the follow-up period. Patients’ diaries, cardiac function (NYHA classification) and adverse events during the follow-up period will be collected every 3 months.

Throughout the study, patients should record diaries when they feel discomfort. Arrhythmia-related symptoms are self-evaluated or evaluated by 7-day Holter monitoring, which has five poles, is weighted 50 g, 2.0 × 2.7 cm, and can record ECG for 7 days. The 7-day Holter instruments were manufactured by BORSAM Co. in Shenzhen, Guangdong Province, China, and provided by the study’s sponsor, Tianjin Institute of Cardiology, Tianjin, China. The attending physicians will also record blood pressure and ECG during each follow-up. Unless necessary, anti-arrhythmic drug therapy will be discontinued during the study according to the attending physicians’ advice for each patient. The design of the study is shown in Fig. 1.

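### The only test named for a continuous outcome is unadjusted; using baseline left atrial dimension as a covariate would give a small, nearly free gain in precision

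*Protocol article*

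**What the plan says.** Item 8 of the Secondary outcome measures section is "changes of left atrial dimension, as measured by ultrasound echocardiography". The Follow-up section plans two measurements: "Ultrasound echocardiography will be performed before the patients enter the study and at the end of the follow-up period".

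The Statistical analysis section gives one rule for continuous data: "Statistical significance will be evaluated by analysis of variance or" the Kruskal–Wallis test. No covariate is mentioned. Its only provision for imbalance at baseline is this: "To adjust for possible baseline imbalances between groups, a Cox proportional hazards model will be used".

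The other outcomes in the article are events (recurrence or progression of AF, clinical events, procedures, deaths). Left atrial dimension is therefore the only listed outcome to which the rule for continuous variables can apply as a treatment comparison.

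**The concern.** The article wants to allow for imbalance at baseline, but the model it names for this handles times to events and cannot be fitted to a continuous change. Left atrial dimension is left with an unadjusted test, although its strongest available predictor, the same dimension at baseline, is to be measured anyway.

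Two things are at stake.

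- **Precision.** Subtracting baseline fixes its coefficient at 1. Unless the two measurements are almost perfectly correlated, that over-corrects and leaves avoidable variance in the comparison.
- **Chance imbalance.** A change score is negatively correlated with its baseline, so an arm that happens to start with larger atria tends to show a larger fall.

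Left atrial dimension is also the only listed outcome that measures atrial structure, and the Background section rests the upstream-therapy idea on atrial remodelling. The sample size was set for the primary outcome, so precision here depends on the analysis chosen.

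**Working it through.** **Inputs from the article**

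- Two echocardiograms per patient, at baseline and at the end (Follow-up).
- Four arms, "initially in a 1:1:1:1 ratio" (Study design).
- Evaluable total 1404 (Sample size calculation), so 1404/4 = 351 per arm. This number was set for the primary outcome.
- Two-sided 5 % level (Statistical analysis).

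**Assumptions**

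The article gives no standard deviation, effect, power or correlation for left atrial dimension, so there is no figure of its own to reproduce. I assume the same standard deviation s at both times and a baseline-to-end correlation r between 0.3 and 0.9.

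**Step 1: variance per patient**

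- Change score: 2(1 − r)s²
- ANCOVA on baseline: (1 − r²)s²
- Ratio: (1 − r²) / [2(1 − r)] = (1 + r)/2

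The extra patients that the change-score analysis needs for equal precision are 2/(1 + r) − 1. The last column is the pairwise power of the change-score analysis, with 351 per arm, at the effect for which ANCOVA has 80 %.

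| Assumed r | Variance ratio (1+r)/2 | Extra patients | Power of change score |
|---|---|---|---|
| 0.3 | 0.65 | 54 % | 62 % |
| 0.5 | 0.75 | 33 % | 68 % |
| 0.7 | 0.85 | 18 % | 73 % |
| 0.8 | 0.90 | 11 % | 76 % |
| 0.9 | 0.95 | 5 % | 78 % |

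Confidence intervals scale with the square root of the ratio. √0.75 = 0.87 and √0.90 = 0.95, so they are about 13 % narrower at r = 0.5 and 5 % narrower at r = 0.8.

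**Step 2: effect of a chance baseline difference**

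Given a baseline difference D between two arms, the change-score estimate is shifted by −(1 − r)D. The ANCOVA estimate is not shifted.

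- Standard error of D with 351 per arm: √(2/351) = 0.0755 s
- 95 % range of D: ±1.96 × 0.0755 = ±0.148 s
- Shift at the edge of that range: 0.5 × 0.148 = 0.07 s at r = 0.5; 0.3 × 0.148 = 0.04 s at r = 0.7

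**Step 3: check by simulation**

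Four arms of 351, no true effect, 20,000 replicates:

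| | r = 0.5 | r = 0.7 |
|---|---|---|
| Variance ratio (theory 0.75, 0.85) | 0.758 | 0.855 |
| Slope of change-score estimate on D (theory −0.50, −0.30) | −0.49 | −0.30 |
| Slope of ANCOVA estimate on D (theory 0) | 0.01 | 0.00 |
| Mean change-score estimate, in s | −0.0006 | −0.0004 |
| Type I error, analysis of variance on change | 0.049 | 0.047 |

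The formulas hold, and the unadjusted test is valid on average.

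**The case against.** The strongest case against is that the sentence on continuous variables is generic. It sits in a paragraph about questionnaire data, never mentions left atrial dimension, and a condensed article may leave covariates to an analysis plan that is not shown. It is true that the article nowhere assigns the test to this outcome by name. But it does state a method for continuous variables, and it does state where baseline adjustment will be used. For the only continuous outcome, what is stated can be improved with data already planned, so this goes beyond missing detail.

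Readers might also infer more than the article supports:

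- **That the baseline echocardiogram is ignored.** The outcome is a change, so baseline enters by subtraction. It is only not used as a covariate.
- **That the comparison is biased.** Allocation is randomised, so the change-score comparison is unbiased over randomisation and keeps its type I error. Only a shift conditional on a chance imbalance remains, and with 351 per arm it is small.
- **That the gain is a known quantity.** Every percentage above depends on an assumed r. At r = 0.9 the gain is 5 %.
- **That the model should be rebuilt around two treatment factors, or adjusted for AF type.** The Primary outcome measures section asks whether the combination does better than either drug alone. A factor model without interaction assumes additivity, which the article does not state. Neither change is needed to repair this point.

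**Conclusion.** The point holds as a minor efficiency improvement. As written, the article offers only an unadjusted comparison for its one continuous outcome, and its adjustment for baseline does not reach that outcome.

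ANCOVA on baseline would cut the variance of a group difference by 10 % to 25 % for an assumed r of 0.8 down to 0.5, and by 5 % at r = 0.9. It would also remove a conditional shift of up to about 0.07 SD at r = 0.5, for baseline differences within their 95 % range. These figures assume equal standard deviations at both times and 351 patients per arm with both echocardiograms.

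The validity of the test and the primary conclusion are unaffected.

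**What to change.** In the Statistical analysis section, state that end-of-study left atrial dimension will be compared across the four randomised groups by ANCOVA, with baseline left atrial dimension as covariate. Report adjusted mean differences with 95 % confidence intervals. Keep Kruskal–Wallis on the change as a sensitivity analysis.

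The listed outcome need not change: with baseline as a covariate, the adjusted group differences are identical whether the response is the end value or the change. The sentence would also settle which of the two is analysed, which the article leaves open. That matters because an unadjusted comparison of end values would be the less efficient choice if r exceeds 0.5: its variance is s² per patient, against 2(1 − r)s² for the change.

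The cost is one sentence. No new data are needed, and the Trial status section says that recruitment is still under way, so the wording can be settled before the outcome data are analysed.
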